#### Intervention fidelity check

MSRS scores will be compared for CT + Memory Support vs. CT-as-usual via independent samples *t* tests. To test the assumption that memory for CT session content improves as a result of CT + Memory Support we will use HLMs to analyze differences in linear rates of change between the two groups on the Patient Treatment Recall Task and Generalization Task delivered during weeks 4, 8, 12 and 16 of the treatment phase and at 6FU and 12FU.

### Additional planned analyses

*Is CT + Memory Support associated with longer time-to-relapse relative to CT-as-usual?* Survival analyses [100] will be conducted. The Kaplan-Meier product limit method will be used to generate survival curves for the two treatment conditions [101]. Cox regression will be applied to test for group differences.
*Are demographics, psychiatric and medical comorbidity, medications and symptom severity moderators?* This will be tested by adding the product of arm and the moderator variable to regression models or HLMs [102, 103]. A significant coefficient for the interaction term would indicate a moderating effect, and will be followed up with graphs to determine the nature of the effect modification [102].
*Does memory for treatment improve simply because memory deficits resolve with successful treatment?* Linear regressions will evaluate whether change in pre-post IDS and pre-post declarative and working memory each independently predict week 4 to post-treatment differences in Patient Recall Task performance. If significant, we will conduct a hierarchical linear regression to evaluate whether pre-post change in IDS scores predicts pre-post change in Patient Treatment Recall Task performance beyond pre-post improvement in memory.
*Memory Support Rating Scale* data will be used to delineate the most effective types and combinations of memory support. Factor analysis will be used to test the structure of the *Memory Support Rating Scale* based on Lee et al. [78]. Associations between patient recall, depression outcomes, and memory support variables will be assessed.
*Number of sessions received* (range 20–26 sessions) will be added as a covariate to control for differences in this across participants.

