### Measures

The primary and secondary outcomes are presented in Additional file 2. Additional file 3 lists all of the measures as well as the timing for administration. Except where specified in Additional file 3, the measures described below will be delivered at each assessment point.

In addition to demographics (age, contact information, gender, race/ethnicity, family, education, employment, living arrangements, government assistance, housing) and assessment of medical history the following measures will be administered:

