### Data analysis

#### Preliminary data evaluation

Missing or aberrant data will be verified. Data will be audited for quality and completeness. Evaluation of distributions detects outliers and ensures that assumptions of planned analyses are met. Baseline differences between groups will be examined (e.g., IQ, demographics, psychiatric and medical comorbidity, medications). Statistical tests will not be used to select covariates in the primary intent-to-treat analysis [90–92]. Instead, the potential influences of baseline differences will be evaluated as moderators. If remedial training is given to a therapist whose adherence to the treatment protocol is not satisfactory, this will be included as a dummy-coded covariate in all analyses.

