#### Multiple testing

We will use alpha = .05 for each primary hypothesis. For multiple testing conducted within each main hypothesis, we will adopt a stepwise multiple comparison procedure that is considered more powerful than the widely used Bonferroni correction [93, 94].

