The relationship between treatment condition and outcome will be moderated by poorer response subgroups; namely, older age, lower IQ, more chronic depression, poorer baseline declarative memory performance and fewer years of education. IQ will be estimated with the NART. Chronicity will be defined as current episode greater than or equal to 2 years [46]. Declarative memory will be quantified as described in Additional file 1. To assess whether Memory Support is more beneficial for any of the patient subgroups, moderation will be tested as an interaction between potential moderator and treatment arm; in the HLMs, the interaction between any of these variables, time, and treatment group will be tested.

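### The additional moderator tests fall outside the plan's multiplicity control and have no exploratory status, yet a significant interaction is read as moderation, even for variables already tested under Hypothesis 3

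*Protocol article*

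**What the plan says.** Five places in the protocol article bear on this.

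- **Multiple testing.** The level is set first: "We will use alpha = .05 for each primary hypothesis". The correction follows: "For multiple testing conducted within each main hypothesis, we will adopt a stepwise multiple comparison procedure". The procedure is not named.
- **Additional planned analyses.** This section lies outside Hypotheses 1 to 3. It asks: "Are demographics, psychiatric and medical comorbidity, medications and symptom severity moderators". On method: "This will be tested by adding the product of arm and the moderator variable to regression models or HLMs". The reading rule is: "A significant coefficient for the interaction term would indicate a moderating effect". Graphs are then to show the form of the effect. No alpha, correction or exploratory label is given.
- **Hypothesis 3.** Five moderators are listed: "namely, older age, lower IQ, more chronic depression, poorer baseline declarative memory performance and fewer years of education". They are tested as moderator by arm and, in the hierarchical linear models (HLMs), together with time.
- **Measures.** The demographic items are listed: "demographics (age, contact information, gender, race/ethnicity, family, education, employment, living arrangements, government assistance, housing". Age and education are among them.
- **Preliminary data evaluation.** Instead of selecting covariates by testing, "the potential influences of baseline differences will be evaluated as moderators". IQ is one of the examples of a baseline difference.

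The article does use an exploratory label, under Exploratory measures, but for certain instruments and not for these analyses.

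**The concern.** The article says how a significant interaction is to be read, and separately limits its error control to a set of tests that does not include these. Followed as written, each additional moderator test can produce a statement of effect modification, and nothing limits the overall chance of a false one.

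The overlap with Hypothesis 3 adds a second difficulty. Age, education and IQ are judged there under the stepwise correction. Age and education can come up again as demographics, and IQ as a baseline difference, both outside that correction. A moderator could fail its protected test and still be reported as a moderating effect from an unprotected one.

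At stake are the trial's statements about which patients benefit more from Memory Support. The primary comparison of the arms is not affected.

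**Working it through.** The article states no error rate for these tests, so there is no figure of its own to reproduce. The check asks what the stated rule implies.

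**Inputs**

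- Level: 0.05 per test, two-sided. This is an assumption, because Additional planned analyses says only that the coefficient is significant. It is the only level in the article: it appears under Multiple testing, for the arm-by-time interactions under Hypothesis 1, and in the Power analysis.
- Number of tests k: not fixed. At the low end, one test per named domain gives k = 4, or k = 5 if psychiatric and medical comorbidity are separated. At a fuller reading, Measures lists 9 demographic items apart from contact information. Adding psychiatric comorbidity, medical comorbidity, medications and severity gives 9 + 4 = 13.
- One outcome, one coefficient per moderator, no true moderation.

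**Chance of at least one false moderator**

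For independent tests this is 1 − 0.95^k. For correlated tests, equicorrelated normal statistics were simulated.

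| k | Independent | Correlation 0.3 | Correlation 0.5 |
|---|---|---|---|
| 4 | 1 − 0.8145 = 18.5% | 17% | 16% |
| 5 | 1 − 0.7738 = 22.6% | not run | 18% |
| 13 | 1 − 0.5133 = 48.7% | 42% | 33% |

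At a correlation as high as 0.8, the figures are 13% for k = 5 and 19% for k = 13. The expected number of false positives at k = 13 is 13 × 0.05 = 0.65. For independent tests the probability first passes one half at k = 14 (51.2%). Several outcomes or time points would raise k.

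Taking age and education out leaves 11 tests on the fuller reading: 1 − 0.95^11 = 1 − 0.5688 = 43.1% if independent. Removing the overlap alone therefore does not settle the first difficulty.

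**With a stepwise correction**

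With a Holm-type procedure across the additional moderators, the first-step threshold is 0.05/k: 0.0125 for k = 4, 0.01 for k = 5 and 0.0038 for k = 13. For independent tests the family-wise rate is then about 4.9% in each case.

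**The two routes for one variable**

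Suppose the age interaction has p = 0.03 and this is the smallest of the five Hypothesis 3 p-values.

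- Under Holm (assumed), the first threshold is 0.05/5 = 0.01. Since 0.03 > 0.01, it fails.
- Under Hochberg (also assumed), it fails unless all five p-values are at most 0.05.
- In Additional planned analyses at an uncorrected 0.05, 0.03 < 0.05, so it is read as a moderating effect.

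The two tests are the same term only outside the HLMs, where both are arm by moderator. In the HLMs, Hypothesis 3 also brings in time, whereas Additional planned analyses describes only the product of arm and moderator. There the variable is the same but the term is not.

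**The case against.** The strongest reply is that this is mostly silence in a condensed article. The threshold, the exact moderator list and the labels may stand in an analysis plan that is not shown. The tests are also set apart under a heading of additional analyses, and leaving such analyses outside family-wise control is a common convention. This has weight, and it is one reason the point is minor. It does not remove the point: the article itself fixes how significance is read and how far the correction reaches. Setting analyses apart as additional but planned does not make them exploratory.

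Some stronger readings are tempting but not supported:

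- *That the article sets an uncorrected 0.05 for these tests.* It does not; that level is inferred.
- *That a significant interaction is treated as proof.* The text says only that it would indicate moderation.
- *That a false moderator claim is more likely than not.* That needs at least 14 independent tests, and the article does not fix the number. The count of 13 is built from a list of items to be collected, not from a list of moderators.
- *That age and education are certainly tested twice by the same test.* The article does not exclude a second test, but does not state one either, and the HLM terms differ.
- *That the baseline-difference moderators are a further set.* The examples largely repeat the list in Additional planned analyses and may describe the same work, so they are not added to k above.
- *That these tests would decide who is offered Memory Support.* Nothing in the article links them to that decision.

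**Conclusion.** The concern holds in limited form. The additional moderator tests have a stated reading rule, lie outside the stated multiplicity control, and are not given exploratory status. The resulting chance of a false moderator per outcome is about three to five times the nominal 5% for 4–5 tests, and about seven to ten times for 13. These figures assume 0.05 per test, no true moderation, and correlation between 0.5 and none.

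The overlap for age, education and IQ is real in the sense that no wording closes the second route. Whether it would be used depends on how the analysts read the text. Severity is low: the defect concerns secondary statements about subgroups and changes no primary efficacy conclusion.

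**What to change.** In Additional planned analyses, and for the baseline-difference moderators in Preliminary data evaluation:

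1. State that these tests are exploratory. Replace the reading rule with a sentence such as: *Interaction estimates will be reported with 95% confidence intervals, and no moderating effect will be claimed from statistical significance alone.*
2. Alternatively, if claims are wanted, list the moderators and apply the stepwise procedure from Multiple testing across them.
3. In either case, state that age, education and IQ are judged as moderators only under Hypothesis 3.

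The change is to wording only and needs no new data. Its cost is that a borderline additional moderator can no longer be reported as established.

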#### Power analysis

Based on the pilot study [34], using Glimmpse [104, 105] for repeated measures design, we took into account the four repeated measurements (pre-treatment, post-treatment, 6FU, 12FU). At an alpha level of 0.05 with 80% power, the sample size is estimated to be 80 for the IDS-SR. We also used G*Power and the Demidenko [106] method to calculate estimated sample size for binary mood outcomes (i.e., remission, relapse). The sample sizes are estimated to be 103 (remission) and 118 (relapse). Finally, Fritz and MacKinnon [107] provide recommendations for mediation sample size, and estimates from pilot data indicate that the recommended sample size is 148. Adding an additional 20% for possible attrition, we propose a sample of 178.

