**Method/design:**

Adults with MDD (*n* = 178, including 20% for potential attrition) will be randomly allocated to CT + Memory Support or CT-as-usual and will be assessed at baseline, post treatment and at 6 and 12 months’ follow-up (6FU and 12FU). We will compare the effects of CT + Memory Support vs. CT-as-usual to determine if the new intervention improves the course of illness and reduces functional impairment (aim 1). We will determine if patient memory for treatment mediates the relationship between treatment condition and outcome (aim 2). We will evaluate if previously reported poor treatment response subgroups moderate target engagement (aim 3).

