Over a 4-year period, adults with MDD (*n* = 178, including 20% for attrition) will be randomly allocated to CT + Memory Support or CT-as-usual and will be assessed at baseline, post treatment and at 6 and 12 months’ follow-up (6FU and 12FU). The first aim is to assess whether the Memory Support Intervention (1) improves the course of illness and (2) reduces functional impairment. Compared to those receiving CT-as-usual, we expect that patients receiving CT + Memory Support will experience greater symptom reduction on measures of course of illness, as defined by the American College of Neuropsychopharmacology (ACNP) Task Force criteria, and on measures of functional impairment. The second aim is to evaluate whether patient memory for treatment mediates the relationship between treatment condition and outcome. Relative to CT-as-usual, we expect CT + Memory Support to be associated with better treatment outcome, and will be mediated by better patient memory for treatment, measured by the Patient Treatment Recall Task. The third aim is to evaluate if previously reported poor treatment response subgroups moderate target engagement. We expect that the relationship between memory support dose and outcome will be positive and stronger among those who are older, have lower IQ, have more chronic depression, have poorer baseline declarative memory performance and have fewer years of education.

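### The sample of 178 covers about 17% attrition, not the 20% stated; at 20% attrition about 142 remain, some 6 below the 148 recommended for the mediation analysis

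*Protocol article*

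**What the plan says.** The Power analysis section of the protocol article gives four sizes:

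- For the continuous depression outcome: "At an alpha level of 0.05 with 80% power, the sample size is estimated to be 80 for the IDS-SR".
- For the binary outcomes, 103 (remission) and 118 (relapse).
- For mediation: "estimates from pilot data indicate that the recommended sample size is 148".

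It then moves from the largest of these to the number to be randomised: "Adding an additional 20% for possible attrition, we propose a sample of 178".

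The total is described twice more. The abstract (Method/design) has "178, including 20% for potential attrition", and the Background repeats the description without the word potential. Both sentences are about the participants who will be randomised. The article gives no other attrition rate.

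**The concern.** A 20% attrition allowance normally means that one in five of those randomised may be lost and the required number will still be left. That calls for dividing the required number by 0.80. Multiplying it by 1.20 gives a smaller total, and the total then falls short of the requirement once 20% are lost.

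Two things are at stake. One is whether the attrition tolerance that readers and the Data Safety and Monitoring Board take from the abstract is correct. The other is the size left for aim 2. The mediation size alone sets the total of 178. The Discussion presents patient memory for treatment as the novel target that the trial is meant to test definitively, so the analysis exposed to the shortfall is not a peripheral one.

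**Working it through.** **Inputs.** All are from the Power analysis section: required sizes 80, 103, 118 and 148; attrition allowance 20%; proposed total 178. The effect sizes, event rates and path coefficients behind the four sizes are not given, so the sizes are taken as stated.

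**1. Reproduce the plan's total.**
- Required size × (1 + 0.20) = 148 × 1.20 = 177.6, rounded up to 178. This matches exactly.
- Required size / (1 − 0.20) = 148 / 0.80 = 185. This does not match; it is 7 more.

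The allowance was therefore added to the target.

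**2. What 178 allows for.**
- Allowance: 178 − 148 = 30 participants.
- As a share of those randomised: 30 / 178 = 16.9%.
- A true 20% of 178 would be 0.20 × 178 = 35.6 participants.

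**3. What remains, by attrition rate.** Remaining = 178 × (1 − rate).

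| Attrition | Remaining | Against 148 |
|---|---|---|
| 10% | 160.2 | met |
| 15% | 151.3 | met |
| 17% | 147.7 | at the limit |
| 20% | 142.4 | short by about 6 |
| 25% | 133.5 | short by about 14 |

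**4. The other sizes.** At 20% attrition, 142 exceeds 80, 103 and 118. The largest of these, 118, would be missed only if attrition passed 1 − 118/178 = 33.7%.

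**5. Effect on mediation power.** The article attaches no power to 148. Assume that 148 gives 80% power at two-sided alpha 0.05 and that power scales as for a single z-test. This is a rough approximation, since an indirect effect is a product of two paths.
- Power at 142 = Φ[(1.960 + 0.842) × √(142/148) − 1.960] = Φ(2.744 − 1.960) = Φ(0.784) ≈ 78%.
- If 148 were instead a 90% size: Φ[(1.960 + 1.282) × √(142/148) − 1.960] = Φ(3.175 − 1.960) = Φ(1.215) ≈ 89%.

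Under either assumption the loss is between one and two percentage points.

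**The case against.** **The 20% may be a top-up and not a loss rate.** Read alone, the Power analysis sentence describes adding 20%, and 20% was added. It does not promise 148 completers. This stands for that one sentence. It does not settle the matter, because the abstract and the Background say that 178 includes 20% for attrition, and the natural meaning is a share of the 178. If a top-up was meant, those two statements are at best imprecise and still need correcting.

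**148 is a recommendation, not a strict requirement.** It rests on pilot estimates and published guidance, and the article itself calls the pilot underpowered. A shortfall of 6 is well within the uncertainty of such a figure. This stands, and it limits the weight of the point. It does not change the arithmetic.

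**Usable data may exceed 142.** The article says that staff will try to collect assessments from participants who discontinue, and the Missing data section has the longitudinal analyses use all available data. Stopping treatment is therefore not the same as dropping out of the analysis. This also stands in part, although the all-available-data statement is made for the longitudinal analyses and does not turn a 16.9% allowance into 20%.

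**A stronger reading on multiplicity.** A reader might infer that the stated sizes also overstate power for Hypothesis 1, because outcomes within a hypothesis are to be tested by a stepwise procedure while the sizing uses alpha 0.05. The article does not support that conclusion. The Multiple testing section says only "we will adopt a stepwise multiple comparison procedure" and does not name the method; a step-up method, whose first comparison is made at the full alpha, fits that description too. The primary outcomes are listed in a supplementary file that is not shown, so the number of tests is unknown. Alpha 0.05 and 80% power are attached explicitly only to the IDS-SR size. These details may also properly sit in the statistical analysis plan.

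**Conclusion.** The point holds as a misstated design figure. The planned 178 retains 148 participants only if attrition is at most 16.9%. At the 20% named in the article, about 142 remain, roughly 6 (4%) below the size recommended for mediation. The arithmetic uses only the article's own numbers and is certain. The drop in mediation power to about 78% is not: it assumes that 148 is an 80% size and that simple scaling applies.

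The consequence is small and confined to aim 2. A reader might infer that the trial is underpowered for its efficacy comparisons. The article's figures do not show that, since 142 still exceeds the sizes stated for the IDS-SR, remission and relapse.

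**What to change.** Correct the statement in three places: the abstract (Method/design), the Background and the Power analysis section.

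- In the abstract and Background, replace the description of 178 as including 20% with a statement that 178 retains 148 for attrition up to about 17%.
- In the Power analysis section, show the step 148 × 1.20 = 177.6. Add that at 20% attrition about 142 participants are expected, that this still meets 80, 103 and 118, and that it falls about 6 below 148.
- State what power, if any, the recommended 148 was meant to give, and report the matching mediation power at 142.

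No extra enrolment is proposed; randomisation began in December 2016 according to the Trial status section. The cost is a few corrected sentences and a slightly less favourable figure for aim 2.

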## Discussion

This study protocol addresses several research priorities. First, following the experimental therapeutics approach [108], this study protocol describes a confirmatory efficacy trial to provide a definitive test of the hypothesis that a novel target—patient memory for the contents of treatment—probed with a novel intervention—the Memory Support Intervention—will improve clinical outcome. Second, a novel intervention derived from basic, non-patient research in cognitive science and education, will be tested in the service of improving outcomes for patients with severe mental disorders. Third, the Memory Support Intervention has been derived to be “transdiagnostic” (relevant to a broad range of mental disorders) and “pantreatment” (relevant to a broad range of types of treatment). However, investigating these possible broader applications seems premature without first establishing efficacy, which is the aim of the study described in this protocol. If the results are promising, future directions will test the applicability to a broad range of biopsychosocial interventions for a wide range of patient populations being treated at various medical and mental health settings.

